### Primary outcome measure

Primary endpoint is operative performance chest drain placement according to the standardized and evaluated OSATS scoring tool as measured by direct observation by the blinded raters during the course. Gaussian distribution of the total score can be assumed.

### Secondary endpoints

Operative performance by gender- and experience-dependent subgroup analyses, time-dependent performance, correlation with extracurricular activities and hobbies, subjective self-assessment as well as possible differences and bias between on-site and video ratings are examined as secondary endpoints [14].

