## Methods and Design

### Objectives

Primary objective of this study is to evaluate training outcome of a structured chest drain training curriculum that comprises elements of serious gaming. Both operative and time-dependent performances of participants are analyzed. Secondary goals include character profiling concerning previous experience and specific extracurricular activities. Thus, participants particularly benefiting from the presented training concept as well as obstacles and positive impulses when training with standardized E-learning platforms might be identified. Evaluation of serious gaming elements in student teaching is also performed to evaluate the potential establishment of such modalities in medical school curricula.

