### Inclusion and exclusion criteria

The inclusion criterion mandates that participants are medical students in their clinical years (3rd–6th year) at Heidelberg University who have completed their 18th year of age. Previous participation in surgical training courses including insertion of chest drains is not an exclusion criterion but will be recorded and analyzed.

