### Assessment

Participants perform chest drain insertion on an accordingly prepared porcine model during the second training session. Performance is videotaped and rated by two different raters on-site using the modified OSATS tool for chest drain insertion (Table 1). The raters are blinded to the training status of the participants. An additional video-based evaluation is performed by a blinded rater according to the same scoring tool. The modified OSATS for chest drain insertion was evaluated in a pilot study and showed good construct validity for distinction between experience levels. Unblinding of raters or employees involved in data analysis and interpretation is not intended. To prevent selection bias, baseline characteristics including age, year of studies, previous experience, gender and hobbies will be compared. Baseline testing on a porcine model is not performed as the hypothesis is that the proposed curriculum, consisting of multimedia training material only, will directly improve performance. The aim of the training curriculum and study is to prepare novices for their first performance of chest drain placement. Baseline testing on a real model could disguise the effect of the training curriculum.

**Table 1 Tab1:** Objective structured assessment of the technical skills score for chest tube insertion

Correct identification of incision location	1 **Poor** The chosen dissection plane deviates tremendously from the suggested site	2	3 **Sufficient** The chosen dissection plane deviates slightly from the suggested site	4	5 **Excellent** 4th/5th intercostal space; mid/anterior axillary line
Correct plane of dissection subcutaneously	1 **Poor** Both distance or execution of tunneling lack accuracy	2	3 **Sufficient** Either distance or execution of tunneling lack accuracy	4	5 **Excellent** Both distance and execution of tunneling are accurate
Blunt dissection on top side of rib	1 **Poor** Flawed dissection; not carried out on top side of rib	2	3 **Sufficient** Solid dissection carried out with minor errors	4	5 **Excellent** Confident cut through the subcutaneous layers and intercostal muscles
Scissors/clamp guarded with other hand during dissection and pulled out without closing the instrument	1 **Poor** Hazardous handling that might affect the patient	2	3 **Sufficient** Improvable handling	4	5 **Excellent** Confident handling of the used instruments

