### Statistical analysis

Mean and standard deviation in case of continuous data, with absolute and relative frequencies for categorical parameters, are used to describe the distributions of all parameters of interest. Possible differences of the primary outcome and OSATS score will be tested using analysis of covariance with intervention group as factor, participants’ self-attributed expertise score as covariate and OSATS score after intervention as dependent variable. Secondary endpoints will be descriptively analyzed according to their respective distribution with t-tests in case of continuous data and chi-square test in case of categorical data. Multiple imputation will be applied to compensate for any missing data. If it is found to be appropriate, graphical statistical methods will be deployed to illustrate findings.

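### The hobby correlation endpoint is given only unadjusted t-tests or chi-square tests, which yield no slope for a graded hobby measure and leave self-attributed expertise as a possible confounder (minor)

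*Protocol article*

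**What the plan says.** The Secondary endpoints section of the protocol article includes "correlation with extracurricular activities and hobbies". The Objectives section gives the purpose: "Secondary goals include character profiling concerning previous experience and specific extracurricular activities".

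The Statistical analysis section has one rule for all secondary endpoints. They are analysed descriptively, "with t-tests in case of continuous data and chi-square test in case of categorical data". It names no correlation or regression method and no covariate for them, and it does not say whether the hobby analysis pools the arms, stays within an arm or compares arms.

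The same section plans the primary comparison as "analysis of covariance with intervention group as factor, participants’ self-attributed expertise score as covariate". Hobbies are collected at baseline, since the Assessment section states that "baseline characteristics including age, year of studies, previous experience, gender and hobbies will be compared". Earlier chest drain training "is not an exclusion criterion but will be recorded and analyzed" (Inclusion and exclusion criteria), so expertise can be expected to differ among participants.

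**The concern.** A method is stated for this endpoint, and it fits poorly in two ways.

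1. **Form.** A t-test compares two means and a chi-square test compares frequencies. If a hobby is recorded on a graded scale, such as hours or frequency, neither returns a correlation or a slope. To apply the rule, either the hobby measure or the OSATS total would have to be cut into groups.
2. **Confounding.** Hobbies are not randomized and may go along with prior expertise. By placing expertise in the primary model, the plan itself treats it as relevant to the OSATS score. An unadjusted test cannot tell a hobby association from an expertise association.

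At stake is how the character profiling is read. A performance difference that reflects prior expertise could be reported as belonging to a hobby. The comparison between the trial arms is not affected.

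**Working it through.** **Inputs.** From Sample size determination: relevant difference 3, SD 5 (reading the ± figure as an SD), α = 0.05, power 0.80, 45 per group. Sidedness is not stated; two-sided is assumed. The article gives no correlation of expertise with hobbies or with OSATS, so every r below is an assumption. The hobby endpoint is read as an association with the OSATS total.

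**Step 1: the plan's own figure.** n per group = 2 × (1.960 + 0.842)² × 5² / 3² = 43.6, so 44 by the normal approximation. The exact t-test gives 44.6, so 45, with power 0.804. The stated 45 reproduces. A one-sided test would need 35, which supports the two-sided reading.

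**Step 2: cost of ignoring arm, if the arms are pooled.** With 1:1 allocation the variance becomes 5² + 3² × ½ × ½ = 25 + 2.25 = 27.25, so the SD is 5.22.
- SE ratio: 5.22 / 5.00 = 1.044, or 4.4% larger.
- Information kept: 25 / 27.25 = 0.917, so 90 students are worth about 83.
- Bias: none expected, because arm is randomized and hobbies are a baseline trait. In a simulation with hobby unrelated to expertise (n = 90, 8,000 runs), the unadjusted test rejected 5.0% of the time.

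**Step 3: confounding by expertise.** Let expertise correlate r with a 50/50 hobby and r with OSATS, and let the hobby have no effect of its own. The hobby–OSATS correlation is then r². The hobby indicator has SD 0.5, so the expected spurious difference is r² × 5 / 0.5 = 2 × r² × 5. The rejection rate is two-sided noncentral t with 45 v 45, 88 degrees of freedom and noncentrality = difference / (SD × √(2/45)).

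| r | Spurious difference (points) | Rejection, SD 5 | Rejection, SD 5.22 |
|---|---|---|---|
| 0.2 | 2 × 0.04 × 5 = 0.4 | 6.6% | 6.5% |
| 0.3 | 2 × 0.09 × 5 = 0.9 | 13.5% | 12.8% |
| 0.4 | 2 × 0.16 × 5 = 1.6 | 32% | 30% |

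Using the SD within hobby groups at r = 0.4, √(25 − 0.8²) = 4.94, raises 32% to 33%.

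**Step 4: cross-check by simulation.** Here the hobby is a split of an underlying normal scale, arm has a 3-point effect, and there are 8,000 runs per setting.

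| Expertise–OSATS | Expertise–hobby (underlying scale) | Unadjusted t-test | Model with arm and expertise |
|---|---|---|---|
| 0.3 | 0.3 | 9.9% | 5.0% |
| 0.5 | 0.3 | 19.6% | 4.9% |
| 0.5 | 0.5 | 43.6% | 4.8% |

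The 9.9% lies below the 12.8% of step 3 because splitting the underlying scale weakens the hobby correlation. The size of the effect depends on the set-up; its direction does not.

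**Step 5: cutting a graded measure.** If the hobby measure were normal and were split at its median, 2/π = 64% of the information would remain. The article states neither condition, so this is illustrative only.

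**The case against.** The case on the other side is substantial, and much of it stands.

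- **A yes/no hobby.** Here the t-test is equivalent to the point-biserial correlation: same p-value, with r = t/√(t² + df). The article does not say how hobbies are recorded, so the mismatch of form holds only for graded measures. The confounding argument applies either way.
- **Arm as a source of error.** A reader might infer that the plan pools the arms and that this makes hobby associations spurious. The article does not say that it pools, and a randomized arm does not bias an association with a baseline trait. If pooling does occur, the cost is a little precision.
- **Is a crude association wrong?** The endpoint asks for a correlation, not an independent effect, and the analysis is called descriptive. Whether students with a given hobby perform better is a fair descriptive question. If a hobby itself raises expertise, adjustment would remove part of a real association. This is why both estimates should be shown rather than one replacing the other.
- **A condensed article.** Model details are often left to a fuller document. That excuses missing detail. It does not remove the mismatch between an endpoint and a method that are both stated here.
- **The stated aim.** Objectives links profiling to identifying "participants particularly benefiting from the presented training concept". That question needs a hobby-by-arm term, which neither the named tests nor a main-effects model supplies. The present point covers only the overall association of hobby with performance.

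**Conclusion.** The point holds in a limited form. The tests assigned to this endpoint give no correlation or slope for a graded hobby measure, and they leave expertise as a possible confounder of any hobby association.

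The confounding could be negligible or material. Rejection is close to nominal at r = 0.2 and roughly two and a half times nominal at r = 0.3. At r = 0.4 it is about six times nominal, and the spurious 1.6 points is just over half of the 3-point relevant difference. These figures assume equal correlations, a 50/50 hobby with no effect of its own, and an SD of 5 to 5.22; the article supports none of the correlations. Readers should not conclude that the hobby results will be spurious, only that the stated tests could not show whether they are.

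Severity is minor: this is a descriptive secondary endpoint, and the primary endpoint, its ANCOVA and the sample size are untouched.

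**What to change.** In the Statistical analysis section, take this endpoint out of the t-test/chi-square rule and add one sentence to this effect:

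*The association of hobbies and extracurricular activities with performance will be estimated by a linear model of the OSATS total on the hobby measure as recorded (uncut), with intervention group as factor. The slope or partial correlation will be reported with a 95% confidence interval, both without and with self-attributed expertise as covariate. These analyses are exploratory.*

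Comparing the two estimates shows how much of a hobby association is shared with expertise. The cost is one or two model degrees of freedom out of 90 participants and a few extra model fits. No new data are needed, since hobbies and expertise are already collected.

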### Statistical analysis

Mean and standard deviation in case of continuous data, with absolute and relative frequencies for categorical parameters, are used to describe the distributions of all parameters of interest. Possible differences of the primary outcome and OSATS score will be tested using analysis of covariance with intervention group as factor, participants’ self-attributed expertise score as covariate and OSATS score after intervention as dependent variable. Secondary endpoints will be descriptively analyzed according to their respective distribution with t-tests in case of continuous data and chi-square test in case of categorical data. Multiple imputation will be applied to compensate for any missing data. If it is found to be appropriate, graphical statistical methods will be deployed to illustrate findings.

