### Randomization

Blocked randomization, stratified by gender, is used to randomly assign participants to each group (1:1 ratio), resulting in one intervention and one control group. Randomization is performed by an employee not involved in training, rating or data collection regarding the present study using opaque, sealed envelopes. As student recruitment to the study will be completed before randomization, any influence of randomization results or subsequent task assignments is considered minimal.

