### Sample size determination

According to results of the pilot study with an identical primary endpoint and conducted in a similar context, group size was determined to be 45 participants randomized to each group. The OSATS for chest drain insertion evaluated in the pilot study will be used as primary endpoint with a relevant mean difference of 3 ± 5 points in the scoring system. Differences can be detected with a significance level α = 0.05 and a power of 1-β = 0.8. Intervention group sizes will exceed this determined sample size.

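### The primary ANCOVA leaves out gender, the only stratification factor; if gender predicts OSATS beyond self-rated expertise, some precision is given up, without bias and with the 80% power still met

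*Protocol article*

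**What the plan says.** All references are to the protocol article.

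- **Randomization:** "Blocked randomization, stratified by gender, is used to randomly assign participants to each group (1:1 ratio". Gender is the only stratification factor named.
- **Statistical analysis:** the primary model is written out in full. It is an "analysis of covariance with intervention group as factor", with participants' "self-attributed expertise score as covariate and OSATS score after intervention as dependent variable". Gender does not appear.
- **Secondary endpoints:** gender returns in "Operative performance by gender- and experience-dependent subgroup analyses". It is also among the baseline characteristics to be compared (Assessment), so it is recorded.
- **Sample size determination:** "group size was determined to be 45 participants randomized to each group", based on "a relevant mean difference of 3 ± 5 points in the scoring system", with "significance level α = 0.05 and a power of 1-β = 0.8".

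The article gives no reason for leaving gender out of the primary model and no figure for a gender effect on OSATS. Because it names the factor, the covariate and the dependent variable, the primary model is fixed here and is not a detail left to an analysis plan.

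**The concern.** The design conditions on gender and the primary analysis does not. Stratified blocks hold the two arms close to balance on gender, so a gender difference in OSATS adds almost nothing to the chance variation of the arm difference. A model without gender does not know this. It leaves the gender variance in the residual and reports a standard error that is too large. Confidence intervals are then wider than they need be, the true type I error lies below the nominal 0.05, and power that the stratification could have delivered is not collected.

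All of this depends on gender explaining some of the OSATS variance that self-rated expertise does not. If it explains none, nothing is lost.

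**Working it through.** **Inputs from the article.** Difference 3 points; SD 5 (reading the ± 5 as the SD); α 0.05; power 0.80; 45 per group, 90 in total. Sidedness is not stated.

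**The plan's own figure.** Two-sided, normal approximation: n per group = 2 × (1.960 + 0.842)² × 5² / 3² = 43.6, so 44. The t-test version gives 44.6, so 45, which matches the article. Power at 45 per group is 0.804 (t). A one-sided test would need only 35, so the two-sided reading is used.

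**Assumptions not in the article.** Let R² be the share of OSATS variance due to gender, beyond expertise. Total SD is held at 5, the arms are balanced on gender, and expertise is taken as unrelated to the outcome.

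**Formulas.** Write k = √(1 − R²).

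- SE reported without gender: 5 × √(2/45) = 1.054.
- True SE under stratification: 1.054 × k. The reported SE is therefore too large by a factor 1/k.
- True type I error without gender: 2 × P(T > 1.988/k), with 87 degrees of freedom.
- Power without gender: P(T′ > 1.988/k), and with gender: P(T′ > 1.988). T′ is noncentral t with noncentrality 3/(1.054 × k), on 87 and 86 degrees of freedom.
- Gender gap implied by R² with a 50/50 split: 5 × √(R²/0.25) = 10 × √R².

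| R² | Implied gender gap (points) | SE too large by | Type I error without gender | Power without → with gender | Points of power forgone |
|---|---|---|---|---|---|
| 0 | 0 | 0% | 5.0% | 0.804 → 0.804 | 0 |
| 2% | 1.4 | 1.0% | 4.8% | 0.806 → 0.811 | 0.5 |
| 5% | 2.2 | 2.6% | 4.45% | 0.810 → 0.823 | 1.4 |
| 10% | 3.2 | 5.4% | 3.9% | 0.816 → 0.843 | 2.7 |
| 15% | 3.9 | 8.5% | 3.4% | 0.823 → 0.863 | 4.0 |

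Power without gender rises slightly with R² because the total SD is held at 5, so the true SE shrinks as gender takes a larger share.

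**Simulation checks.**

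- *Without the expertise covariate* (90 participants, stratified 1:1 allocation, assumed 60/40 gender split, 20,000 runs per setting): type I error 4.5%, 3.8% and 3.3% at R² of 5%, 10% and 15%. Power was 0.811 → 0.824, 0.816 → 0.842 and 0.824 → 0.863.
- *With the expertise covariate in the model* (blocks of 4, 50/50 split, 10,000 runs per setting): with no gender effect, type I error was 0.048 and power 0.80 under either model. At a 2-point gender gap (R² 4%), type I error without gender was 0.040 and power went from 0.805 to 0.816. At a 3-point gap (R² 9%), it was again 0.040, and power went from 0.811 to 0.835. With gender in the model, type I error stayed between 0.045 and 0.051 in every setting, including gaps of up to 5 points. A 60/40 split gave the same pattern.

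**The case against.** The strongest reply is that the effect is conditional and its size unknown. The article gives no gender effect on OSATS, and with none the omission costs nothing. The larger scenarios are also demanding: R² of 10% or 15% means a gender gap of about 3.2 or 3.9 points, above the 3 points that the trial treats as relevant for the intervention. Nothing in the article supports a gap of that size. At about 2 points, the loss is about 1 point of power. All of this stands, and it limits the point to an efficiency matter.

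The covariate matters too. If self-rated expertise relates to both gender and OSATS, it absorbs part of the gender variance and the loss shrinks further. The calculations do not test this, because they treat expertise as unrelated to the outcome. This also stands.

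A reader might draw stronger conclusions that the article does not support:

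- *That the trial is underpowered or has no margin.* The planned model gives power of about 0.80 or more in every setting. What is forgone lies above the target. The sample size section also says that group sizes will exceed 45, although the abstract gives 90 in total, the figure used here.
- *That the stratification shows gender was expected to be a strong predictor.* Stratifying also secures balanced arms within the planned gender subgroups, which is reason enough.
- *That the t-tests for continuous secondary endpoints must be replaced.* The article describes those analyses as descriptive, so no confirmatory error rate is at stake.

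What the reply does not remove is the mismatch itself. The article fixes a primary model without the factor by which it randomizes, and gives no reason.

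**Conclusion.** The point holds as a conditional loss of efficiency. If gender predicts OSATS beyond self-rated expertise, the planned ANCOVA reports too large a standard error and tests below its nominal level. For an assumed gender share of 2% to 5% of the variance, the true type I error is about 4.8% to 4.5%, and about 0.5 to 1 point of power is forgone. At 10% the figures are about 3.8% and 2 to 3 points. At 0% there is no loss.

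The treatment estimate is not biased and false positives are not inflated. These figures rest on SD 5, a difference of 3 points, 90 participants, a two-sided test, near balance on gender within arms, and gender shares that are assumptions. To say without qualification that the test is conservative would go beyond the article.

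**What to change.** State the primary model as OSATS total score = intervention group + gender (stratification factor) + self-attributed expertise score, before the data are analysed. The cost is one sentence and one degree of freedom (86 instead of 87 for the residual). Gender is already recorded, and the sample size does not change because it was computed without any covariate. If gender turns out not to matter, power is practically unchanged (0.804 with or without it). The secondary-endpoint t-tests can stay as they are.

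### The aim of finding who benefits most from the app is paired with t-tests, which do not estimate differential benefit; an arm-by-subgroup interaction does

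*Protocol article*

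**What the plan says.** Four statements in the protocol article bear on this point.

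- **Objectives.** After describing a profile of previous experience and extracurricular activities, the article hopes to identify "participants particularly benefiting from the presented training concept". The wording is tentative: such participants may be found.
- **Secondary endpoints.** The list opens with "Operative performance by gender- and experience-dependent subgroup analyses". It gives no subgroup sizes and no cut-point for experience.
- **Statistical analysis, secondary endpoints.** "Secondary endpoints will be descriptively analyzed according to their respective distribution with t-tests in case of continuous data"; categorical data get a chi-square test.
- **Statistical analysis, primary outcome.** The only model named is "analysis of covariance with intervention group as factor, participants’ self-attributed expertise score as covariate". It contains main effects only.

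No arm-by-gender, arm-by-experience or arm-by-hobby term appears anywhere. The article does not say whether the t-tests compare arms within a subgroup or compare subgroups with each other. It also gives no rule for declaring that one subgroup benefits more.

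**The concern.** Who benefits more is a question about effect modification: does the difference between arms vary with experience, hobbies or gender? A two-sample t-test could be applied here in two ways, and neither answers that question.

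- **Arm against arm within each subgroup.** This yields two separate p-values. That one falls below 0.05 and the other does not is no test of whether the two effects differ, because each subgroup has much less power than the whole trial.
- **Subgroup against subgroup.** This shows who scores higher, not who gains more from the app. The Assessment section rules out a baseline test on the porcine model, so individual gain cannot be measured either.

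At stake is a stated secondary goal. A reader of the results could be told that the app suits one kind of student when the effect is the same in both. The primary comparison and the sample size are not affected.

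**Working it through.** **Inputs (Sample size determination).** A "relevant mean difference of 3 ± 5 points in the scoring system", read as difference 3 and SD 5; "significance level α = 0.05 and a power of 1-β = 0.8"; and "group size was determined to be 45 participants randomized to each group". Sidedness is not stated, so two-sided is assumed. Subgroup sizes are not given, so a range of splits is shown.

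**1. The plan's own figure.** The normal approximation gives n = 2 × 5² × (1.96 + 0.84)² / 3² ≈ 43.6, so 44 per group. With the noncentral t, 44 per group gives power 0.795 and 45 gives 0.804. The stated 45 is reproduced. A one-sided test would need 35, which supports the two-sided reading.

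**2. Two equal subgroups, same 3-point effect in both.** There are 22.5 students per arm in each subgroup. Each within-subgroup t-test has power p = 0.503. The chance that exactly one is significant is 2p(1 − p) = 2 × 0.503 × 0.497 = 0.50. A simulation of 40,000 trials (23 and 22 per arm) gave 0.5005.

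**3. Unequal subgroups, same 3-point effect.** The chance is p₁(1 − p₂) + p₂(1 − p₁).

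| Split per arm | p₁ | p₂ | Exactly one significant |
|---|---|---|---|
| 18 / 27 | 0.417 | 0.581 | 0.51 |
| 15 / 30 | 0.355 | 0.628 | 0.54 |
| 11.25 / 33.75 | 0.274 | 0.680 | 0.58 |
| 9 / 36 | 0.224 | 0.709 | 0.62 |

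**4. Equal subgroups, other common effects.**

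| Common effect (points) | 0 | 1 | 2 | 3 | 4 | 5 | 6 |
|---|---|---|---|---|---|---|---|
| Exactly one significant | 0.095 | 0.18 | 0.38 | 0.50 | 0.38 | 0.17 | 0.05 |

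For equal subgroups 2p(1 − p) cannot exceed 0.50, so the planned effect happens to sit at the maximum.

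**5. The interaction test under the same conditions.** Its simulated false-positive rate was 4.7% to 5.1% for splits of 23/22, 30/15 and 36/9 per arm, with a common effect of 0 or 3 points.

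**6. What the interaction test can detect.**

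- Equal subgroups: SE = 5 × √(4/22.5) = 2.11 points.
- Power for a 3-point interaction: Φ(3/2.11 − 1.96) = Φ(−0.54) ≈ 0.30.
- Interaction needed for 80% power: 2.80 × 2.11 ≈ 5.9 points.
- Smallest estimate that would be significant: about 2 × 2.11 ≈ 4.2 points.
- 20/80 split: SE = 5 × √(2/9 + 2/36) = 2.64 points, and 2.80 × 2.64 ≈ 7.4 points for 80% power.

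These figures ignore any precision gained from the expertise covariate and from groups larger than 45.

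**The case against.** The case on the other side has four parts.

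**The analyses are called descriptive.** The objective is tentative, and no rule turns a p-value into a claim about a subgroup. This stands against any statement that the trial will report false subgroup differences. It does not rescue the method: a descriptive label lowers the strength of a claim but does not make a t-test estimate the right quantity.

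**The t-test sentence is generic.** It covers all secondary endpoints, including correlations and rater comparisons that it does not literally fit, and a condensed article may leave detail to a fuller plan. The ANCOVA sentence could also be stretched to cover OSATS by subgroup. It is therefore an inference that arms will be compared within subgroups. But the article does name a method, and neither that method nor the ANCOVA as described contains an interaction.

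**Gender is not part of the benefit objective.** This stands. The Objectives tie benefit to previous experience and extracurricular activities, and gender enters only through the secondary endpoints. Comparing men's with women's performance is a legitimate description. It becomes a problem only if it is read as differential benefit.

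**The remedy has low power.** True, at about 30% for a 3-point interaction. That limits what can be concluded by any method; the interaction interval shows the limit openly.

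A reader might infer that half of all such analyses will mislead. The documents do not support that. The figure needs the planned effect in both subgroups, roughly equal subgroups, within-subgroup testing and a significant-in-one-only rule, and the last three are not stated. A reader might also infer that interactions below 6 points cannot be detected. That is wrong too: 5.9 points is the 80%-power value for equal subgroups, not a threshold.

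**Conclusion.** The concern holds in a conditional form. The stated method does not fit the stated goal under either reading of the t-test, and no interaction term is named.

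The size depends on how the tests are used. With a two-sided 5% level, SD 5, 45 per arm, two equal subgroups, a common 3-point effect and the significant-in-one-only rule, a false subgroup difference appears about 50% of the time, against about 5% for an interaction test. Over common effects of 0 to 6 points the figure is about 5% to 50%. At 3 points with a 20/80 split it is about 62%.

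This is a change that should be made, but it is not a threat to the trial's main result.

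**What to change.** In the Statistical analysis section, state that any claim of differential benefit will rest on an interaction estimate.

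- Add an arm-by-experience term to the primary ANCOVA, with the matching main effect where it is not already in the model. In separate models, add an arm-by-hobby term, and an arm-by-gender term if a claim about gender is intended. Enter the interactions one at a time.
- Report each interaction estimate and the within-subgroup effects with 95% confidence intervals, labelled exploratory.
- State that power is low: with equal subgroups the SE is about 2.1 points, power is about 30% for a 3-point interaction, and 80% power needs about 5.9 points. Uneven subgroups need more, for example about 7.4 points at 20/80. Do not write a fixed 6-point detection limit into the plan.
- Keep comparisons of performance between subgroups, if wanted, as descriptions of who scores higher.

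The cost is analysis wording only. Gender is a stratification factor, and previous experience and hobbies are already collected, so no new data are needed. The downside is wide intervals.

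### Time-dependent performance is compared between arms by an unadjusted t-test although the primary OSATS comparison is adjusted for self-attributed expertise: a valid choice, but one that may give up precision and is inconsistent with the primary model (minor)

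*Protocol article*

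**What the plan says.** In the protocol article, the Statistical analysis section says that the primary outcome will be "tested using analysis of covariance with intervention group as factor, participants’ self-attributed expertise score as covariate". The next sentence turns to everything else: "Secondary endpoints will be descriptively analyzed according to their respective distribution with t-tests in case of continuous data". Categorical data get a chi-square test. No covariate is mentioned for any secondary endpoint.

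The Secondary endpoints section lists gender and experience subgroups of operative performance, followed by "time-dependent performance, correlation with extracurricular activities and hobbies, subjective self-assessment as well as possible differences and bias between on-site and video ratings". Of these, time-dependent performance and self-assessment are the ones that lend themselves to a plain comparison of the two arms. The Objectives section, directly after stating the primary objective, adds: "Both operative and time-dependent performances of participants are analyzed".

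Two other sections bear on whether expertise is balanced. Randomization is in blocks and stratified by gender alone. On earlier training, the eligibility section says: "Previous participation in surgical training courses including insertion of chest drains is not an exclusion criterion but will be recorded and analyzed".

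**The concern.** By adjusting the OSATS score for self-attributed expertise, the plan treats that score as related to how well a student performs. Expertise is not a stratification factor, and students with earlier chest drain training may take part, so the arms can differ in expertise by chance. The primary analysis takes such a difference into account. The time comparison, made on the same students, does not.

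Two things could follow. The confidence interval for time may be wider than it needs to be. And the score and time results would rest on different models, so part of any contrast between them could reflect the choice of model. The covariate is already required for the primary analysis, and the article gives no reason for using it in one comparison and not the other.

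**Working it through.** **Inputs from the article.** 45 participants per arm; OSATS difference 3 with 5 read as the standard deviation (SD), so 0.6 SD; significance level 0.05, taken as two-sided because the side is not stated; power 0.8 (all from Sample size determination).

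**Assumptions.** The correlation r between self-attributed expertise and time-dependent performance is not given, so a range is used. Time-dependent performance is taken to be continuous and compared between arms.

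**1. The plan's own figure.** Normal approximation: n = 2 × (1.960 + 0.842)² × (5/3)² = 2 × 7.85 × 2.78 = 43.6, so 44 per arm. The exact two-sample t-test gives 44.6, so 45, with power 0.804. The stated 45 is reproduced by an unadjusted two-sided test of the OSATS. A one-sided test would need 35 and does not match. The article gives no target difference for time.

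**2. Precision.** In SD units of the outcome, the unadjusted standard error (SE) of the arm difference is √(2/45) = 0.211. Adjustment multiplies it by √(1 − r²). The unadjusted sample size giving the same precision is 45/(1 − r²).

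| r | √(1 − r²) | SE reduction | Adjusted SE | Equivalent n per arm |
|---|---|---|---|---|
| 0.1 | 0.995 | 0.5% | 0.210 | 45.5 |
| 0.2 | 0.980 | 2% | 0.207 | 46.9 |
| 0.3 | 0.954 | 5% | 0.201 | 49.5 |
| 0.5 | 0.866 | 13% | 0.183 | 60.0 |

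The table leaves out the cost of estimating the slope. For a normally distributed covariate this multiplies the variance by about 1 + 1/(90 − 4) = 1.012, or the SE by √1.012 = 1.006. At r = 0.1 that cancels the gain (0.995 × 1.006 = 1.001). At r = 0.5 it hardly matters (0.866 × 1.006 = 0.871).

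**3. Chance imbalance.** The difference between arms in mean expertise has an SD of √(2/45) = 0.211 SD of the expertise score. An imbalance of that size moves the unadjusted outcome difference by r × 0.211: 0.021, 0.063 or 0.105 SD at r = 0.1, 0.3 or 0.5. This is not a second effect on top of step 2. At r = 0.5 the squared unadjusted SE is 0.211² = 0.0444, and it splits into 0.105² = 0.0111 from imbalance and 0.183² = 0.0333 from the rest. The t-test's standard error already contains the imbalance.

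**4. Validity and agreement.** In simulations of 20,000 trials per setting with 45 per arm, the t-test rejected in 0.048 to 0.051 of trials when there was no effect. Applying the t-test and the covariance model to the same outcome gave different significance verdicts as follows.

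| r | No effect | Difference of 0.6 SD |
|---|---|---|
| 0 | 1% | 2% |
| 0.3 | 3% | 7% |
| 0.5 | 5% | 12% |

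The 0.6 SD is the OSATS planning value and serves here only as an illustration for time.

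**The case against.** The strongest reply is that nothing here is wrong. After randomisation the unadjusted t-test is unbiased and keeps its error rate, as step 4 confirms. The plan calls the secondary analyses descriptive and attaches no power or confirmatory claim to them. The gain depends on an r that the article does not give, and nothing in it links expertise to procedure time. Experience is also handled elsewhere: baseline characteristics are compared and experience subgroups are planned, so a visible imbalance would be reported. All of this stands, and it limits the point to a minor one. It does not remove it, because the unadjusted test is a stated choice rather than a detail left to a fuller document, and a better alternative is at hand.

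A reader might infer more than the documents support:

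- **That chance imbalance biases the time result in addition to the lost precision.** Step 3 shows these to be the same thing.
- **That a contrast such as a better score with slower performance would be an artefact.** Score and time are different outcomes and can truly differ.
- **That time is co-primary because the Objectives section mentions it beside operative performance.** The outcome sections place it among the secondary endpoints.
- **That self-assessment would gain most from adjustment.** The article does not say when the expertise score is taken or whether it is distinct from the self-assessment endpoint. If they overlap, the model would adjust an outcome for itself.
- **That the hobby endpoint will be a confounded t-test pooled over arms.** The Secondary endpoints section speaks of correlation and does not describe such a test, and the article gives no figures from which a false difference could be calculated.

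**Conclusion.** The point holds as a minor matter of precision and consistency, chiefly for time-dependent performance. The analysis as written is valid, but it leaves unused a covariate that the primary analysis already requires. With 45 per arm the reduction in standard error would be about 0.5% at r = 0.1, 5% at r = 0.3 and 13% at r = 0.5, and it is negligible at r of about 0.2 or less. These figures rest on an assumed r, a roughly linear relation between expertise and the outcome, and an expertise score that the intervention does not affect. No conclusion about the primary endpoint depends on this.

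**What to change.** In the Statistical analysis section, state that time-dependent performance will be compared between arms with the model used for the primary outcome: arm as factor and self-attributed expertise as covariate, on the log scale if the times are skewed. Report the adjusted difference with its 95% confidence interval (a ratio, if the log scale is used). The t-test may stay as a supporting description.

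Apply the same model to self-assessment only if the expertise score is a separate measure taken before the intervention, and say in the text whether it is.

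The change takes one or two sentences and no new data. It uses one degree of freedom, and if expertise turns out to be unrelated to time, the standard error grows by about 0.6% (step 2). The wording should be settled before outcomes are examined by arm, so that the choice of model cannot depend on the result.
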